Research into mobile apps as a method to intervene for psychiatric disorders are promising (e.g. Donker et al., 2013; Eysenbach et al., 2011; Saeb et al., 2015). App-based mental health interventions based on e.g. CBT principles have shown to be effective in reducing mental health symptoms with within-group and between-group intention-to-treat effect sizes ranging from  $d = 0.29 - 2.28$  and  $0.01 - 0.48$  at post-test and follow-up, respectively in a review of Donker et al. (2013). Advantages are better accessibility and participant retention, real-time progress monitoring, portability, and flexibility. As far as we know, one study has investigated the effectiveness of VRET using a mobile application for fear of spiders. Results showed a reduction in anxiety levels (Piercey et al., 2012). Another study investigating VRET on a smartphone has recently found VRET to be effective at reducing spider phobia symptoms and non-inferior to traditional one-session exposure therapy (Miloff et al., 2019).

Recently, we have explored the feasibility and efficacy of ZeroPhobia: Acrophobia, a VRET delivered through a smart phone app using Google cardboards for fear of heights (Donker et al., 2019). The randomized controlled trial (RCT) demonstrated large effect sizes and ZeroPhobia: Acrophobia was rated user-friendly. The aim of the proposed project is to test a (similar) low cost, scalable, and evidence-based solution for aviophobia and arachnophobia symptoms through exposure therapy by integrating VR technology with a smart phone app in two separate RCTs. Both interventions will be tested for its effectiveness in reducing anxiety symptoms and user-friendliness. ZeroPhobia: Arachnophobia will differ

from ZeroPhobia: Aviophobia in that it will be a guided VRET, in order to determine whether drop-out rates are lower than previous, unguided trials of ZeroPhobia. The study will be of a randomized controlled trial (RCT) design and will be conducted amongst adults from the general Dutch populations with aviophobia and arachnophobia symptoms.

We hypothesize that both ZeroPhobia applications will effectively reduce anxiety symptoms as well as be rated as user friendly.

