#### **4.3 Sample size calculation**

Aviophobia: An effect size of Cohen's  $d = 0.80$  was found from a meta-analysis of VR treatments for fear of flying (Fodor, 2018). Because ZeroPhobia: Aviophobia is a complete self-help treatment with rudimentary VR glasses, we have taken a slightly more conservative effect size of 0.70 as the starting point for the power calculation. To demonstrate a difference between the experimental and control condition with a standardized effect size of  $d = 0.70$  (tested on both sides), an alpha of 0.05 and a statistical power (1-beta) of 0.80, we have 34 respondents in each condition required (68 respondents in total). Taking into account a drop-out rate of 40% (Donker et al., 2019), we need a total of 96 respondents ( $n = 48$  per condition).

Arachnophobia: An effect size of Cohen's  $d = 1.11 / 1.12$  was found from a meta-analysis of VR treatments for different phobias, including fear of spiders (Opris et al., 2012,

Powers et al., 2008). Because ZeroPhobia: Arachnophobia is a complete self-help treatment with rudimentary VR glasses, we have taken a slightly more conservative effect size of 0.80 as the starting point for the power calculation. To demonstrate a difference between the experimental and control condition with a standardized effect size of  $d = 0.80$  (tested on both sides), an alpha of 0.05 and a statistical power (1-beta) of 0.80, we have 26 respondents in each condition required (52 respondents in total). Taking into account a dropout rate of 40% (Donker et al., 2019), we need a total of 72 respondents ( $n = 36$  per condition).

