### **8.1.3 Other study parameters (if applicable)**

- Demographic variables (gender, age, education level, marital status, employment status).
- System Usability Scale (SUS; Bangor et al., 2008): 10 items about user friendliness of the app. The SUS is composed of 10 statements that are scored on a 5-point scale of strength of agreement. Final scores for the SUS can range from 0 to 100, where higher scores indicate better usability. This means that products that are at least passable have SUS scores above 70, with better products scoring in the high 70s to upper 80s. Truly superior products score better than 90. Products with scores less than 70 should be considered candidates for increased scrutiny and continued improvement and should be judged to be marginal at best. Reliability is good (Bangor et al. 2008). This questionnaire will be completed at post-test.
- User-friendliness of ZeroPhobia as a treatment will be in part measured with the 6-item self-report treatment expectation and satisfaction scale called the

Credibility/Expectancy Questionnaire (CEQ; Devilly & Borkovec, 2000). The CEQ measures expectations of the participants before the start of the treatment. This questionnaire will be used alongside the post-test SUS and NEQ to determine if ZeroPhobia did in fact meet expectations.

- User-friendliness will also be measured using single item questions directly asking about the user experience of ZeroPhobia and the realism of the VR environments. This also includes one open question asking for any other feedback on the app a participant would like to give.
- Igroup Presence Questionnaire (IPQ; Schubert, Friedmann and Regenbrecht 2001), a 14-item questionnaire, which assess realism and “presence” in the VR environment. Each of the items has five response categories from fully disagree (1) to fully agree (5). Chronbach`s alpha is good ( $\alpha = .73$ ). This questionnaire along with some open questions about user experience of the VR environment will be completed at post-test.
- Ecological Momentary Assessment: One question about current anxiety level during exposure in VR
- Usage data from the ZeroPhobia app: frequency and duration of practice during exposure in VR, frequency and duration of time spent in the modules.
- Flight usage questions, including when was the last time you flew on an airplane, how many times have you flown in the past 3/12 months and how long was each of these flights?

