### **10.3 Other study parameters**

Continuous variables (IPQ, SUS, CEQ, NEQ) will be presented as mean, standard deviation, and minimum and maximum number of observations. Categorical variables will be presented in terms of frequency numbers and percentages (e.g. demographic variables). Descriptive statistics of demographics and clinical outcomes will be compared between the experimental and control condition. The quantitative analysis will be performed on an intention-to-treat basis following the per protocol analysis according to CONSORT recommendations and SPIRIT guidelines for reporting results (Chan 2013a, 2013b; Eysenbach et al., 2011). For the analyses on continuous scales including user data, repeated measures analyses of variance (ANOVA) are used. Multiple imputation will be used in dealing with missing data, assuming this is "at random" (Brunton-Smith et al., 2014). STATA version 14 will be used for the analyses. The best static analysis procedure to perform the analyses for this RCT will be reviewed before the data is analysed.

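### Section 10.3 imputes the post-test-only usability and presence scores (SUS, IPQ) under an at-random assumption, which pulls the usability result towards the ratings of those who responded

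*Protocol*

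**What the plan says.** User-friendliness is a stated hypothesis in section 1: "We hypothesize that both ZeroPhobia applications will effectively reduce anxiety symptoms as well as be rated as user friendly". It is also a secondary objective in section 2.

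Section 8.1.3 lists the System Usability Scale (SUS, 0 to 100) and the Igroup Presence Questionnaire (IPQ) among the other study parameters. Table 1 places both at post-test only. On reading the SUS, section 8.1.3 says that "products that are at least passable have SUS scores above 70" and that "Products with scores less than 70 should be considered candidates for increased scrutiny".

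Section 10.3 first gives the descriptive summary: "Continuous variables (IPQ, SUS, CEQ, NEQ) will be presented as mean, standard deviation, and minimum and maximum number of observations". It then calls for an intention-to-treat analysis and adds "Multiple imputation will be used in dealing with missing data", on the assumption that data are missing at random. It does not restrict the imputation to the app arm or to people who opened the app, and it names no sensitivity analysis.

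Section 4.3 plans both trials with an allowance for loss. For aviophobia it reads "Taking into account a drop-out rate of 40" per cent, and the same rate is used for arachnophobia.

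**The concern.** At-random imputation is credible when the observed data explain who is missing. For the SUS that is doubtful. A hard-to-use app is a plausible reason to stop and then ignore the post-test, so the chance of a missing score may depend on the score itself. There is no earlier SUS value to condition on, and Table 1 places the single-item user-experience questions at post-test too, so they are missing for the same people.

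The IPQ raises a further problem. Section 5.1 confines VR use to one of the six modules. Someone who stopped before that module, or never opened the app, has no VR presence to report, and an imputed score stands for nothing. The same holds for the SUS of someone who never used the app.

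At stake is the usability conclusion for both apps. An overall mean could look acceptable partly because less satisfied users did not answer. Section 10.3 also assigns repeated-measures ANOVA to continuous scales, which a scale measured once cannot use. This suggests that the efficacy wording was carried over without being fitted to these measures.

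**Working it through.** **Inputs from the protocol.** Drop-out allowance 40% in each trial; 48 (aviophobia) and 36 (arachnophobia) randomised to the app (section 4.3). SUS reference value 70 (section 8.1.3).

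**Assumptions.** The protocol gives no SUS mean, SD or responder/non-responder gap. All such values below are assumed.

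**Step 1: the plan's own totals.** 68 × 1.4 = 95.2, rounded up to 96; 52 × 1.4 = 72.8, stated as 72. The totals therefore come from multiplying by 1.4. The loss they can absorb is 1 − 68/96 = 29% and 1 − 52/72 = 28%. I use 40% as the planned share and 29% as a lower comparison.

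**Step 2: expected SUS returns at 40% loss in the app arm.** 48 × 0.6 = 28.8, about 29 responders and 19 missing. 36 × 0.6 = 21.6, about 22 responders and 14 missing.

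**Step 3: size of the overstatement.** Let R be the responder mean, D the responder-minus-non-responder gap and m the missing share.

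Overall mean = (1 − m)R + m(R − D) = R − mD.

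If nothing in the imputation model predicts SUS, the imputed mean is R, so the overstatement is mD:

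| D (points) | m = 0.40 | m = 0.29 |
|---|---|---|
| 10 | 4.0 | 2.9 |
| 20 | 8.0 | 5.8 |
| 30 | 12.0 | 8.7 |

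**Step 4: where the overall mean reaches 70.** Setting R − mD = 70 gives D = (R − 70)/m. At m = 0.40:

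| R | Gap D | Non-responder mean | Check |
|---|---|---|---|
| 75 | 12.5 | 62.5 | 0.6 × 75 + 0.4 × 62.5 = 70 |
| 78 | 20 | 58 | 0.6 × 78 + 0.4 × 58 = 70 |
| 80 | 25 | 55 | 0.6 × 80 + 0.4 × 55 = 70 |

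**Step 5: what a better imputation model recovers.** A large simulation assumed 40% missing, SUS SD 15, and odds of non-response multiplied by e for each SD of lower SUS. The gap came to about 0.824 SD, or 0.824 × 15 = 12.4 points, and 0.4 × 12.4 = 4.9 points of overstatement among responders. At-random imputation with one auxiliary variable then left:

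| Correlation of auxiliary with SUS | Remaining overstatement (points) |
|---|---|
| 0 | 4.9 |
| 0.3 | 4.6 |
| 0.5 | 3.9 |
| 0.7 | 2.8 |

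Imputation reproduces responders' ratings exactly only when nothing predictive enters the model. Otherwise it removes part of the bias.

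**Step 6: bounds on a proportion.** If 75% of the 28.8 aviophobia responders scored above 70 (assumed), that is 21.6 people. Counting every non-responder as a low scorer gives 21.6/48 = 45%. Counting every one as a high scorer gives (21.6 + 19.2)/48 = 85%.

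**The case against.** The other side has real points, and they limit what can be claimed.

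- **Drop-out is not the same as a missing SUS.** A reader might infer that 40% of app users will have no score. The 40% is a trial-wide planning figure from an earlier trial, not split by arm. Section 8.6 keeps following people withdrawn from treatment, and section 8.3 schedules the post-test at six weeks even if the modules are unfinished, with an e-mail and then a phone reminder. The arachnophobia app is guided partly to see whether drop-out is lower. Only post-test non-responders are affected.
- **Imputation can use other data.** A reader might infer that non-responders are simply given completers' scores. The app logs frequency and duration of use (section 8.1.3), and these could enter the model, whose content may properly sit in a statistical analysis plan that is not at hand. This stands, but step 5 shows that even a strong auxiliary leaves part of the bias.
- **70 is not a pass mark.** Section 8.1.3 offers it as a way of reading product scores; no decision rule is attached to it.
- **Other measures exist.** The CEQ, NEQ, single-item questions and an open question also inform user-friendliness. However, the CEQ as described there concerns expectations before treatment, and the user-experience items share the post-test gap.
- **The summary may use observed data only.** Section 10.3 does not say whether the descriptive mean is taken before or after imputation. An observed mean would err in the same direction.

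The protocol also says that the analysis procedure will be reviewed before analysis, but it names no alternative.

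**Conclusion.** The concern holds in a limited form. Section 10.3 fixes an at-random imputation for two scales measured once, after use of the app, where non-response may depend on what is being measured. If non-responders rate the app lower, the imputed SUS mean is too favourable by up to mD. At 40% missing that is 4 points for a 10-point gap and 8 for a 20-point gap; at 29% it is 2.9 and 5.8. The direction rests on the assumption that poor usability lowers response, which is plausible but not shown in the protocol. For the IPQ, and for anyone who never used the app or the VR, imputation is inappropriate whatever the mechanism.

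The documents do not support saying that either app would pass through attrition alone, or that the true proportion of satisfied users is 45%. That figure is a worst-case bound, with 85% at the other end on the same inputs. The primary efficacy comparison is not touched by this point. It is a cheap improvement to a secondary objective.

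**What to change.** In section 10.3:

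1. Take the SUS and IPQ out of the multiple imputation.
2. Report both as observed, among app-arm participants who used the app (for the IPQ, the VR), with the number responding out of all randomised to the app.
3. Show logged app usage for responders and non-responders side by side.
4. Add a tipping-point analysis giving the non-responder mean at which the overall SUS would fall to 70, naming 70 as the interpretive benchmark of section 8.1.3 and not as a success rule.
5. If the proportion of all app-randomised participants who responded and scored above 70 is shown, label it a worst-case bound and do not make it the main result.

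No new data are needed, because usage is already logged and post-test response is already recorded. The cost is a few lines of analysis text, a little more output and possibly a less favourable usability statement.

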### **10.4 Interim analysis (if applicable)**

No interim analyses will be performed.

## 11.2 Recruitment and consent

Advertisements with a call to participate in a VR mobile app study for aviophobia/arachnophobia will be shared through several media outlets (Radio, TV), websites (e.g. Fonds Psychische Gezondheid, Angst Fobie en Dwangstichting, Google Adwords, Facebook), mental health institutes (e.g. Stichting Valk for Aviophobia) and in magazines (e.g. de Ingenieur). When a person is interested to participate in the study, s/he can use the URL of the website provided in the advertisement to be directed to the study homepage of ZeroPhobia. On this page, information about the study is provided, including eligibility criteria.

If the person thinks they fulfill the inclusion criteria and is interested to participate in the study, they will be invited to click on a link ('aanmelden'), which opens a new e-mail window with our research team as the addressee. In this way, participants are able to contact us to show interest. Information (name and email of the participant) will be received by the researcher, with which we will email more information about the study, specifically the consent form, the participant information letter, and the CMO brochure. In this email, we will ask that if they are still interested in participating after reading these materials, for them to use the provided link to a secure survey.

This survey will allow them to provide a physical mailing address, so hard copies of consent and informational materials can be mailed to them. Screening questions will also include items about age, Dutch fluency, whether or not they are currently receiving psychiatric services for their phobia, and either the FAS or FSQ (duration of 15 minutes). This screener is given prior to official consent in order to save ineligible participants time and prevent unnecessary baseline data from being collected. If participants do not meet inclusion criteria, an automatic email will be sent to them notifying them of their exclusion and the reasoning of such. If participants are eligible, a trigger email will be sent to the researchers to let us know they meet criteria to

participate. Ineligible participant's screening data will be deleted once ineligibility has been determined.

If eligible and still interested, the research assistant will send the patient information letter and informed consent form to their home address with a return envelope. If necessary, the researcher will remind them by email to complete the informed consent (2 reminders in total). The informed consent form will be sent to each participant. The participant will be instructed to sign the consent form and mail it back to us. Once received, we will sign the consent form as well and then make a copy of the consent form. This copy will be mailed back to the participant to keep for their own records.

Upon receiving informed consent, the researcher will send a second survey link to participants via email to complete a baseline measurement. In this baseline measurement, demographic variables (gender, level of education, marital level), FAS/FAM (aviophobia) or FSQ/SPQ (arachnophobia), PHQ, BAI and WSQ will be measured (duration of 20 minutes).

If necessary, the researcher will remind them by email to complete the baseline measurement (2 reminders in total). After the baseline has been completed, participants will be randomized by an independent researcher. The research assistant will notify the participant of which condition they have been randomized to, either the intervention condition or the waitlist condition.

#### **Objection by minors or incapacitated subjects (if applicable)**

Not applicable.

### **11.3 Benefits and risks assessment, group relatedness**

Participants may benefit from their participation in terms of expected reductions in anxiety and depression levels. It is expected that participation will help improve clinical care. Additionally, similar interventions have previously shown to be effective in reducing anxiety and symptoms of specific phobia via VRET through a mobile application (Piercey et al., 2012). Research of another ZeroPhobia app (for fear of heights (acrophobia)) found that self-guided VRET via a smartphone app did effectively reduce specific phobia symptoms (Donker et al., 2019). Furthermore, other research into mobile apps as a method to intervene for psychiatric disorders are promising (e.g. Donker et al., 2013; Eysenbach et al., 2011; Saeb et al., 2015).

Previous studies in similar samples have shown that studies with VRET can safely be carried out, without a significant risk for unwanted effects (e.g. Bouchard et al., 2006; Emmelkamp et al., 2002; Krijn et al., 2004; Piercey et al., 2012). Specifically, previous research on ZeroPhobia: Acrophobia demonstrated that ZeroPhobia can be safely carried out without

serious adverse effects – e.g. no participants reported any injuries during VR use or unbearable anxiety levels during exposure or any other modules of the app (Donker et al., 2019).

One possible risk of participation is the induction of too much fear. In order to treat specific phobia, a certain level of fear is necessary. Without this, treatment would not be effective (Wolitzky-Taylor et al., 2008). In order to assuage the risk of inducing too much fear too quickly, the VR exposure environment is designed to use gradual exposure. This means that subjects start with relatively easy levels of feared situations which induces a small amount of fear. When this situation becomes less fearful, they move on to the next level. In this way, fear levels are manageable. Additionally, participants set their own level of fear induction before beginning an exposure. In this way, they have control over how intense the exposure is, again reducing the risk of inducing too much anxiety.

If a participant does experience extreme distress due to selecting a VR exposure that is too challenging for them, they are instructed to remove their VR glasses. Participants are informed that they are allowed to exit the VR environment or the app at any time, simply by removing their glasses and/or closing the app. In case of an undesirable emotional reaction associated with the modules or VR exposures, the participant is instructed to contact the research assistant, who will inform at least one experienced and licensed clinician ([name] or [name]). This clinician will be available to the participant to provide support if necessary or desired.

Similarly, cybersickness may also occur when using VR technology. Again, participants are informed of this, and told to remove their glasses if this happens. By removing their glasses, levels of high distress or cybersickness are immediately reduced, making it effective in mitigating risk.

Another possible risk associated with this study is a participant feeling imbalanced when using VR technology, causing a risk of falling. To reduce the chance of this occurring, participants are instructed to remove all sharp or otherwise dangerous objects away from their vicinity. They are also told to sit down while using VR. If they do choose to stand, we notify them that they should hold on to something sturdy to help maintain balance. The risk for falling is greater for individuals 65 and older, and for this reason, individuals of this age range are excluded from participating.

A final risk associated with this study is the possibility of questionnaires evoking distress. Questionnaires cover a range of topics, most focused on measuring anxiety symptoms. It is possible that reading and responding to these questionnaires could evoke some distress. However, these instruments are crucial in drawing conclusions about the feasibility and effectiveness of the intervention. In case of an undesirable emotional reaction both during the intervention as well as during the follow up assessments, the participant is instructed to contact

the research assistant, who will inform at least one experienced and licensed clinician ([name] or [name]). This clinician will be available to the participant to provide support if necessary or desired.

If after completion of ZeroPhobia: Fear of Flying participants still have questions about their aviophobia or wish for further treatment, then we will encourage them to contact 'Stichting VALK.' Stichting VALK is an anxiety treatment institute that was created in 1990 in cooperation with University of Leiden, KLM, and Schiphol Airport ([www.valk.org](http://www.valk.org); [[contact]](mailto:[contact])).

Participants will not be withheld regular care during the study; a participant who wishes to seek additional help for their phobia or any other medical issues will not be prevented from doing so.

